## Introduction

Worldwide, liver cirrhosis ranks as the 11th most common cause of death. In 2019, it accounted for an estimated 1.48 million deaths, reflecting an 8.1% increase since 2017 [1]. The distribution of cirrhosis etiologies and their prevalence varies across countries, largely due to differences in lifestyle factors such as alcohol consumption, obesity, and the risk of viral hepatitis. In Europe, alcohol-related liver disease (ARLD) is currently the leading cause of cirrhosis-related deaths [2].

Liver cirrhosis is the end stage of chronic liver disease of all causes, resulting from sustained inflammation that progresses to fibrosis and, ultimately, liver failure. The progression of liver cirrhosis is divided into a compensated stage, characterized by an absence of specific symptoms and apparent complications, and a decompensated stage featuring one or more severe complications such as ascites, hepatic encephalopathy, infection, renal dysfunction, and variceal bleeding [3]. At this stage, the patient often experiences fatigue, nausea, malnutrition and increasing frailty due to loss of muscle mass. This transition from compensated to decompensated liver cirrhosis significantly worsens health-related quality of life (HRQoL) scores [4, 5], while median survival decreases dramatically from approximately 12 years to just two years [6, 7]. Patients with decompensated liver cirrhosis experience some of the highest rates of unplanned hospital admissions, with 1.5 to 3 liver-related admissions per year [8–12].

The current management of decompensated liver cirrhosis focus on symptom relief, the prevention of further complications, and, if possible, liver transplantation, which remains the only curative option [7–14]. According to the World Health Organization, palliative care should be integrated alongside life-prolonging medical treatment as part of a cohesive approach to care, focusing on enhancing the quality of life for patients and their informal caregivers facing the challenges of serious illnesses. Palliative care aims to prevent and relieve suffering through early identification, assessment, and treatment of physical, psychosocial, and spiritual symptoms and concerns [15].

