### Intervention elements

The intervention is delivered alongside standard care and integrated into patients’ regular clinical appointments. In all participating settings, standard care involves routine follow-up of patients with cirrhosis by a team of hepatologists and specialised liver nurses. Following an admission due to decompensated cirrhosis, patients are routinely offered planned follow-up in an outpatient clinic.

The initial palliative care conversation is conducted by a hepatologist in collaboration with a specialised liver nurse. Alternatively, the conversation may be conducted solely by the liver nurse. Subsequent conversations are conducted by either a hepatologist or a liver nurse after 4–10 weeks, and at 6, 12, 18, 24, 30, and 36 months, or until withdrawal from the study or death. Extra visits may be scheduled if clinically indicated or if the patient or informal caregivers request additional support or planning.

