### Effectiveness outcomes

#### Primary outcome

*Healthcare system burden*, measured as the number and length of hospital admissions from the initial visit to death or study exit. Data on health care utilisation will be prospectively recorded by registering events since the last visit at each study visit and compared to a recent historic cohort of a similar size from the involved centers.

Hospital admissions will be categorised into three mutually exclusive groups:

*Liver-related admissions*: inpatient stays of ≥ 24 h due to complications of liver cirrhosis, including variceal bleeding and other bleeding related to portal hypertension, hepatic encephalopathy, spontaneous bacterial peritonitis, hepatorenal syndrome, alcoholic hepatitis, ascites, infection, electrolyte imbalances, increasing frailty, sarcopenia, or poor nutritional status.*Non-liver-related admissions*: inpatient stays of ≥ 24 h for conditions not directly related to cirrhosis.*Short admissions*: hospital stays of < 24 h, excluding admissions in which paracentesis is the sole intervention.

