### Implementation outcomes

An overview of the process indicators and methods of measurement for the feasibility study and process evaluation are presented in Table 1.

**Table 1 Tab1:** Overview of process indicators and methods of measurement and data collection

Domain	Method	Process indicators	Data sources
Reach and uptake	Descriptive quantitative evaluation	Number of patients referred for the intervention Number of patients included of all eligible Referral patterns	Screening data
Effectiveness	Preliminary quantitative evaluation of endpoints in Phase 2 and quantitative evaluation of endpoints in Phase 3 Cost-effectiveness analysis Cost-utility analysis	Number and length of hospital admissions Patient reported outcomes Change in caregiver burden Staff time, training, materials Healthcare utilization QALYs gained	Medical records PRO-Pall EQ-5D-5 L ZBI Danish DRG tariffs EQ-5D-5 L
Adoption		Proportion of sites offering the intervention	Information from study sites
		Differences in implementation between implementation sites	
*Implementation:* Feasibility: *The degree to which the intervention can be carried out in a given setting.*	Mixed-method evaluation Descriptive quantitative evaluation Qualitative evaluation	Resource utilisation Palliative care planning processes No. of invitation leaflets handed out to participants and families No. of palliative conversations per participant No. of informal caregivers participating in palliative conversations. No. of PRO-Pall questionnaires completed for each palliative conversation. No. of medical interventions. No. of patients referred to palliative care teams No. of patients referred to hospices No. of patients referred to municipal offers (exercise, nutrition, alcohol treatment, etc.) Patient experience Caregiver experience Healthcare personnel experience	Self-developed questionnaire with open-ended questions on experiences with palliative care, pre-study training, and the intervention
*Fidelity: The degree to which the intervention was implemented as intended.*			Informal conversations with health care professionals
Acceptability and Appropriateness: *The perception among implementation stakeholders that a given intervention is agreeable*,* palatable*,* or satisfactory.*			Semi-structured interviews informal caregivers and patients
			Medical records
			Semi-structured qualitative interviews

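### The visit-based recording of admissions does not by itself cover the time from the last visit to death or study exit, and the historic cohort cannot be recorded that way

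*Protocol article*

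**What the plan says.** The Primary outcome section defines the outcome as healthcare system burden, "measured as the number and length of hospital admissions from the initial visit to death or study exit". The next sentence gives the method of capture. Utilisation will be "prospectively recorded by registering events since the last visit at each study visit and compared to a recent historic cohort". That cohort is to be about as large and to come from the same centres. How admissions are obtained for the historic cohort is not described.

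Intervention elements sets the later conversations "after 4–10 weeks, and at 6, 12, 18, 24, 30, and 36 months, or until withdrawal from the study or death". Extra visits are allowed if clinically indicated or requested. No closing step at death or exit is mentioned.

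Table 1, under Implementation outcomes, gives the data sources for the effectiveness domain as "Medical records PRO-Pall EQ-5D-5 L ZBI Danish DRG tariffs", among others. The indicators in that row include number and length of admissions. The table gives no time window and does not mention the historic cohort.

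**The concern.** The window and the capture rule do not match. The rule looks back from a visit to the one before it. A patient who dies has no further visit, so the rule, followed as written, never reaches the stretch between the last visit and death. For a patient who withdraws, the same holds for the stretch from the last visit to the exit date.

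The historic cohort cannot have been measured by this rule, because it had no LiverCare visits. Some retrospective source is unavoidable there, and such a source would ordinarily contain admissions close to death. The trial is not randomised, so equal measurement of the primary outcome in the two groups is one of the few protections available, and adjustment for patient characteristics does not restore it. The uncovered period is also the end of life, when hospital use may well be highest and where a palliative intervention may be expected to act. Number and length of admissions also feed the cost-effectiveness analysis.

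**Working it through.** **Plan's own figures.** The article gives no estimate of incomplete capture, so there is none to reproduce. The yardstick comes from Sample size: 7 days/year in the historic cohort, a hypothesised reduction of 2 days/year and an SD of 7, giving 199 participants. Read as a per-group number with two-sided 5% and 80% power (neither is stated), the t-test solution is 194, close to 199. The point here does not depend on that number.

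**Inputs from the article.** Visits at 0, 4–10 weeks (7 weeks used), then 6, 12, 18, 24, 30 and 36 months. 7 days/year and a 2-day target. In the Introduction, on decompensation, "median survival decreases dramatically from approximately 12 years to just two years".

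**Assumptions.** Survival is exponential. All scheduled visits are attended and there are no extra visits. There is no withdrawal. Stays after the last visit are never recovered in the intervention group and are fully counted in the historic cohort. The true effect is nil.

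**Step 1, deaths and person-time.** Hazard h = ln 2 / 2 = 0.3466 per year.
- Probability of death before 36 months: 1 − 2^(−1.5) = 0.646.
- Mean person-time per patient to death or 36 months: 0.6464 / 0.3466 = 1.865 years.

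**Step 2, uncovered time.** Averaging (time of death − last scheduled visit) over deaths before 36 months gives 0.219 years, or 2.6 months.
- Uncovered time per patient: 0.6464 × 0.2191 = 0.1417 years.
- Share of person-time: 0.1417 / 1.865 = 7.6%.

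**Step 3, constant admission rate.** 7 × 0.076 = 0.53 days/year, which is 27% of 2 days.

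**Step 4, higher rate before death (assumption).** Let the rate be k times the base rate in the last three months of life of those who die before 36 months. Per patient, time in those three months is the integral from 0 to 3 of min(t, 0.25)·h·exp(−ht) = 0.151 years. Of this, 0.111 years falls after the last visit. With the overall mean held at 7 days/year, the share of days missed is (0.1417 + (k−1) × 0.111) / (1.865 + (k−1) × 0.151).
- k = 2: 0.2527 / 2.016 = 12.5%, or 0.88 days/year (44% of target).
- k = 3: 0.3637 / 2.167 = 16.8%, or about 1.18 days/year (59% of target).

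**Step 5, person-time also stopped at the last visit.** The observed rate is 7 × (1 − share of days missed) / (1 − 0.076).
- k = 1: 7.00, a spurious reduction of 0.
- k = 2: 7 × 0.875 / 0.924 = 6.63, a reduction of about 0.4 days/year.
- k = 3: 7 × 0.832 / 0.924 = 6.30, a reduction of about 0.7 days/year.

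**Step 6, sensitivity.** With median survival of 1 to 4 years and k of 1 to 3, and person-time counted to death, the range is 0.3 to 2.0 days/year (14% to 98% of target).

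**Step 7, records reviewed through death or exit.** Nothing is missed, and the spurious reduction is 0.

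**The case against.** A reader might infer that terminal stays are lost in the intervention group and that the primary result is therefore biased towards benefit. The article does not support that. Its outcome window expressly runs to death or study exit, and nowhere does it say that visits are the only source. Table 1 lists medical records, and the two places can be read together: one says when events are registered, the other where they come from. Nor can the direction be called certain, because the historic cohort's source, time origin and end of follow-up are not described. For withdrawals the window ends at study exit, so only the time from the last visit to the exit date is at stake.

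The size is also conditional. It assumes that nothing is recovered, the terminal multipliers come from outside the article, and extra visits in deteriorating patients would shorten the gap. All of this stands.

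It can also be said that an article leaves such operational detail to the full protocol. That carries less weight here. The article is not silent: it states a capture rule for the primary outcome, and the rule does not reach the end of the window defined one sentence before. Table 1 does not settle the matter, because it is equally compatible with staff consulting records only when a patient attends.

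**Conclusion.** The point holds as a mismatch and an open risk. It does not show that data are lost. The described capture rule does not by itself cover the interval from the last visit to death or exit, it cannot apply to the historic cohort, and no stated step makes the two cohorts comparable on this.

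If terminal stays go unrecovered in the intervention group and are counted in the historic cohort, the comparison leans towards the intervention. At a two-year median survival the spurious reduction is then about 0.5 to 1.2 days/year with person-time counted to death, and 0 to 0.7 days/year with person-time stopped at the last visit. The upper ends rest on an assumed threefold terminal rate. Against a 2-day target, this is large enough to require a change before the analysis.

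**What to change.** Take number and length of admissions in both cohorts from the same source (hospital records or the patient register). Use the same admission definitions and one extraction rule, from the index date to death or study exit, and include the interval after the last visit. Keep visit-based registration as a check. Reword the Primary outcome section and Table 1 so that both describe this. Follow-up beyond withdrawal is optional and not needed for this fix.

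The cost is one record extraction per patient at exit and possibly an addition to the data-access approval. If the sponsor already works this way, one clarifying sentence is enough.

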**Methods:**

The LiverCare study is a multi-center, mixed-method, pragmatic, non-randomised clinical study with a hybrid type 1 effectiveness-implementation design. The study is conducted in hepatology departments across four hospitals in three of Denmark’s five regions. It is guided by the British Medical Research Council and Reach, Effectiveness, Adaption, Implementation, Monitor frameworks and includes both a feasibility study and a mixed-method process evaluation.

The LiverCare intervention is grounded in a palliative approach, emphasising open, exploratory palliative care conversations. The intervention is integrated into routine outpatient care and the palliative care conversations are delivered by hepatologists and liver nurses who attended a specially designed course within palliative care. Eligible participants are adults with decompensated liver cirrhosis of any etiology who meet at least one general and one disease-specific palliative care indicator, assessed using the Supportive and Palliative Care Indicators Tool. Informal caregivers are invited to participate in the intervention.

Palliative care conversations are initiated following a formal invitation and continue after four to ten weeks and then every six months up to 36 months or until study withdrawal or death. The primary outcome is healthcare utilization, defined as the number and length of hospital admissions, compared to a historic cohort. Secondary outcomes include outpatient contacts, symptom burden, quality of life, and caregiver burden. The study also includes cost-effectiveness and cost-utility analysis.

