## Sample size and statistical methods

### Sample size

The study aims to include 240 patients and 100 informal caregivers, based on sample size calculations for the most significant outcomes and to accommodate expected attrition.

The Healthcare System Burden will be measured as the number and length of admissions. Patients with cirrhosis spend an average of seven days per year in hospital [39]. Health care utilization data from the intervention group will be compared to a recent historical cirrhosis cohort. For the sample size calculation, we assumed the historical cohort will have an average of seven days in hospital per year and hypothesize that the intervention will cause a reduction of two days/year with an assumed SD of 7 days. Hence, 199 participants are required (STATA BE 18.5). With an estimated attrition rate of 20%, we aim to include 240 patients [40, 41].

Caregiver burden will be measured using the 22-item ZBI (range 0–88). A change of 5 points is considered realistic and clinically relevant. Based on previous studies, this change can be detected with 100 informal caregivers if the standard deviation (SD) of the change is around 14 [35, 36].

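### The primary outcome names two measures, number and length of admissions, but only hospital days per year is sized, and nothing says which measure decides the trial

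*Protocol article*

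**What the plan says.** The outcome is defined by two measures in three places.

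- Abstract, Methods: "The primary outcome is healthcare utilization, defined as the number and length of hospital admissions, compared to a historic cohort".
- Primary outcome section: the burden on the healthcare system is "measured as the number and length of hospital admissions from the initial visit to death or study exit".
- Sample size section: "The Healthcare System Burden will be measured as the number and length of admissions".

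Under the Primary outcome heading the article adds: "Hospital admissions will be categorised into three mutually exclusive groups". These are liver-related stays and non-liver-related stays of at least 24 h, and short stays under 24 h. Stays for paracentesis alone are taken out of the short group and counted as outpatient contacts.

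The calculation in the Sample size section uses one quantity. For the comparator, "we assumed the historical cohort will have an average of seven days in hospital per year". The hypothesis is that "the intervention will cause a reduction of two days/year with an assumed SD of 7 days". No effect or SD is given for the number of admissions.

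The Statistical methods section lists a t-test or a Wilcoxon-Mann-Whitney test for numerical data and 95% confidence intervals. It gives no lead measure, no order of testing, no rule that both measures must improve and no division of alpha.

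**The concern.** A primary outcome should yield one answer, or come with a rule that turns several results into one. Here two results share primary status without a rule.

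This matters in two ways. First, if a favourable result on either measure could be presented as the primary finding, each tested at 5%, the chance of a false claim is above 5%. Second, the two measures can disagree. Total days are the number of admissions times the mean length of stay. An intervention that avoids some admissions, but leaves the remaining stays longer, can lower the count while total days stay the same or rise. The article does not say whether such a trial would have met its primary objective.

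The comparison is non-randomised and uses a historic cohort. That makes it more important to fix the deciding result before the data are seen.

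**Working it through.** **Inputs.** From the Sample size section: comparator mean 7 days per year, reduction 2 days per year, SD 7 days, 199 required, 240 planned. From the Primary outcome section: a historic cohort of similar size, so allocation is taken as 1:1. Assumed, because not stated: two-sided alpha 0.05 (in line with the 95% confidence intervals) and 80% power.

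**Step 1: what the 199 covers.** For a comparison of two means,

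n per group = 2 × SD² × (z for alpha + z for power)² / difference² = 2 × 49 × (1.960 + 0.842)² / 4 = 192.3, so 193.

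The t-test version gives 193.3, so 194. The stated 199 is within 3% of 194. At 199 per group the power is 81.3%. Read as a total over both groups, 199 would give only 52%, so it is best read as a per-group figure. It corresponds to a single comparison of hospital days per year.

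**Step 2: false-positive chance if either measure could count.** With two tests, each two-sided at 0.05, and no true effect:

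- Independent tests: 1 − 0.95² = 9.75%. This is the ceiling for non-negative correlation.
- Correlated tests, from the bivariate normal distribution, 1 − P(both |Z| < 1.96):

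| Assumed correlation | Chance of at least one p < 0.05 |
|---|---|
| 0.5 | 9.1% |
| 0.7 | 8.3% |
| 0.8 | 7.8% |
| 0.9 | 7.0% |
| 0.95 | 6.5% |

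The article gives no correlation between the two measures, so the range is shown instead of one figure.

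**Step 3: what keeping both measures would cost.**

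- *Either one sufficient, alpha split equally (0.025 each).* The days measure needs 2 × 49 × (2.241 + 0.842)² / 4 = 232.9, so 233 per group. Allowing for 20% loss, 233 / 0.80 = 291.3, so 292. At 199 per group the power for days falls from 81.3% to 72.9%.
- *Both must succeed.* Alpha is not inflated, but power cannot be computed, because there is no effect or SD for the number of admissions.
- *Days alone as primary.* The requirement stays at 193 to 194 per group, which the stated 199 already covers.

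The stated size therefore fits a single primary measure, and the only measure it can be checked against is hospital days per year.

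**The case against.** The best defence is that number and length are two components of one burden measure. Their product is total days, and the Sample size section moves straight from the two-part definition to annual days. On that reading there is one primary endpoint, loosely described. Test order and multiplicity rules may also sit in an analysis plan that is not shown. Part of this stands: no sentence says that success on either measure is enough, so the false-positive figures are conditional. But the choice of the primary variable belongs in the protocol. This article does make that choice, three times, as two measures, and then sizes one. A reader cannot tell that total days decides.

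It is also fair that the inflation is small. Count and days are likely to be strongly correlated, and at 0.95 the rate is about 6.5%.

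Two stronger readings are tempting, and the document supports neither.

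- *Six primary comparisons.* A reader might cross two measures with three admission groups and infer a much larger error rate. The article says only that admissions are categorised. It does not make each group an endpoint or say that each is tested. The groups may simply define what counts, for example by removing paracentesis-only stays.
- *Biased attribution of cause.* A reader might infer that unblinded staff classify admissions as liver-related in one cohort while records are used in the other. The article does not say who assigns cause or how the historic cohort is classified. Table 1 lists medical records among the sources for the effectiveness domain. This would in any case be a different issue from the choice of endpoint.

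**Conclusion.** The point holds at two measures. Number and length are both named primary, only hospital days per year is sized, and the deciding result is not identified. If either could count at an assumed two-sided 5%, the false-positive chance is about 6.5% to 9.1% for assumed correlations of 0.95 to 0.5, with a ceiling of 9.8% for non-negative correlation. The stronger reason to act is that a trial with fewer but longer stays would have no defined primary conclusion. This should be corrected. It is not a fatal flaw, because the existing sample size already supports a single primary measure at about 81% power under the stated effect and SD.

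**What to change.** In the Abstract, the Primary outcome section and the Sample size section, name one primary endpoint: total hospital days per person-year across all admissions, which is the quantity already used for sizing. State whether stays under 24 h count towards it; the Sample size section does not say whether its seven-day figure includes them. Make number of admissions a key secondary endpoint. Report the liver-related, non-liver-related and short groups descriptively with confidence intervals.

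The cost is a change of wording, plus a matching registry change if the registered outcome is worded the same way. No new data or patients are needed. The small downside is that number of admissions loses primary status. If the investigators want to keep both as primary, they should state the decision rule, give an effect and SD for the count, and redo the sample size.
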